### Follow-up plan

There are four follow-up visits via medical records or telephone calls if women achieve clinical pregnancy.

Around 13 weeks of gestation, information on the ongoing pregnancy and any first-trimester pregnancy complications, such as early abortion and ectopic pregnancy, will be collected.

Around 29 weeks gestation, the second-trimester pregnancy complications—such as hypertensive disorders of pregnancy, gestational diabetes mellitus, and late abortion—will be recorded.

At the time of delivery, information on obstetrical and perinatal complications, as well as neonatal medical records, is acquired.

The final visit follows the postpartum complications and neonatal complications 6 weeks after delivery.

Timely follow-up visits should be conducted to reduce the number of participants who discontinue or deviate from intervention protocols.

Women will be asked about adverse events at each visit. Adverse events (AEs) are defined as any adverse medical problems that arise during the research period, without regard to their connection to the intervention. AEs in this study will be collected systemically and divided into study-related AEs and non-study-related AEs, which will be judged by clinicians at the time of recording every clinic visit.

All AEs will be recorded in detail and reported. Once any adverse reaction occurs during medication use, the drug will be stopped immediately. Serious AEs will be reported to the principal investigator immediately, and appropriate measures will be initiated instantly. The ethics committee will determine whether the AE is likely to have been associated with the experimental drug. The following conditions are considered serious AEs: death, life-threatening, severe or permanent disability, congenital malformation or birth defect, neonatal death within 6 weeks of delivery, or any other event that the local principal investigators deem serious. Adverse events must be timely noted and reported.

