Several retrospective studies have found that letrozole administration in FET increased clinical pregnancy rate (CPR) and LBR [3–6] and decreased the incidence of hypertensive disorders of pregnancy in women with PCOS compared to the programmed regimen [7]. However, a single-centre, randomized, controlled clinical trial found no significant difference between the two regimens in terms of CPR and embryo implantation rate [8]. According to a recent meta-analysis, the ovulation induction regimen increased the LBR and reduced the risk of miscarriage, preeclampsia, and preterm labour in patients with PCOS when compared to the programmed regimen. In the subgroup analysis, on the other hand, they evaluated different ovulation regimens and found that the letrozole ovulation regimen achieved a higher CPR [9]. Therefore, further prospective research is required to confirm whether the letrozole ovulation regimen can achieve better pregnancy outcomes than the programmed regimen.

This study is a multi-centre randomized controlled clinical trial. It compares the efficacy and safety of the letrozole ovulation regimen with the programmed regimen in women with PCOS undergoing FET.

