### Randomization and blinding

A computer-generated random list is generated by SPSS 16.0 (SPSS Inc., Chicago, IL, USA). The statisticians will upload the random list into the online database’s central grouping system and maintain the random list absolutely confidential. The list is not accessible to the researchers. They are only given the group number when a patient is enrolled. Letrozole tablets or estradiol valerate tablets will be given to participants. Since the trial is open-label, neither the participants nor the physicians are blind to the group information, while all the generated data in the trial will be analysed by blinded independent biostatisticians.

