## Discussion

This study will compare the efficacy and safety of the letrozole ovulation regimen with the programmed regimen in women with PCOS undergoing FET. We intend to enrol at least 148 subjects from 6 academic IVF centres in China. Approximately half of the subjects have been enrolled by the time of manuscript preparation since enrollment started in September 2022. The result of this multi-centre randomized trial will provide strong evidence for the strategy of FET in patients with PCOS.

Recently, a freeze-all and delayed FET policy has gained widespread support [13–15]. Our previous study demonstrated that FET contributed to a higher rate of live birth, a lower incidence of OHSS, and a higher birth weight of the singleton in patients with PCOS when compared to fresh embryo transfer [1]. The reason for a higher success rate of FET may be that the endometrium is typically spared from the adverse effects of supraphysiological concentration of estrogen.

The first choice of endometrial preparation in FET for PCOS patients is still controversial. Women who use the programmed regimen have a lower embryo implantation rate and higher incidence of caesarean delivery, preeclampsia, and postpartum haemorrhage in contrast to the natural regimen [16, 17]. These outcomes could be attributed to the application of high-dose exogenous estrogen and a lack of endogenous luteal support. According to a retrospective study conducted in America, LBR was comparable between the letrozole FET group and the programmed FET group among anovulatory women [18]. However, a Chinese retrospective study indicated that the ovulation induction regimen would be the better choice [19]. Furthermore, the letrozole ovulation regimen could reduce the incidence of hypertensive disorders of pregnancy, gestational diabetes mellitus, and large for gestational age infants in patients with PCOS [20–22]. These benefits may be related to promoting the expression of integrins, leukaemia inhibitory factor, L-selectin, and the formation of cytosolic convexity induced by letrozole, which improves endometrial tolerance and helps patients achieve better pregnancy outcomes [23, 24].

Whether the letrozole ovulation regimen could achieve better pregnancy outcomes in PCOS patients is of great clinical significance. This study is expected to provide a reliable answer.

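### The serious adverse event list has no hospital-admission criterion, so whether an admission is classed as serious and reported immediately depends on local judgement at six open-label sites

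*Protocol article*

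**What the plan says.** All of the following is from the protocol article.

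- **Follow-up plan, definition.** The serious-event list opens with "The following conditions are considered serious AEs: death, life-threatening, severe or permanent disability, congenital malformation or birth defect" and closes with "neonatal death within 6 weeks of delivery, or any other event that the local principal investigators deem serious". Inpatient admission or prolonged stay is named neither here nor elsewhere in the article.
- **Follow-up plan, consequence.** "Serious AEs will be reported to the principal investigator immediately, and appropriate measures will be initiated instantly". All other adverse events are to be recorded in detail and reported in a timely way, but immediacy is attached only to the serious ones.
- **Randomization and blinding.** "Since the trial is open-label, neither the participants nor the physicians are blind to the group information". Only the analysts are blinded. Design and setting names six hospitals.
- **Background.** On the aim: "It compares the efficacy and safety of the letrozole ovulation regimen with the programmed regimen".
- **Discussion.** Women on the programmed regimen are said to have a "higher incidence of caesarean delivery, preeclampsia, and postpartum haemorrhage in contrast to the natural regimen". The Background and Discussion also associate letrozole cycles with fewer hypertensive disorders of pregnancy.
- **Follow-up plan and Outcome and outcome assessments.** Four follow-ups collect pregnancy, obstetric, postpartum and neonatal complications in women who reach clinical pregnancy, which is defined by a gestational sac inside the uterus. These complications are secondary outcomes.

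**The concern.** The maternal harms that motivate the safety aim often bring a woman into hospital without killing her, disabling her or immediately threatening her life. As the list stands, such an admission meets no fixed criterion. It becomes serious only through the last clause, "or any other event that the local principal investigators deem serious", which gives no threshold. Six sites can apply six thresholds, and the people applying them know the allocation.

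Two things are at stake. First, an admission that is not labelled serious is not covered by the immediate-reporting sentence. Second, any table of serious events would mix fixed criteria with site habit and would be hard to interpret in a trial of 148 women.

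The gap matters most for women without an intrauterine pregnancy. The scheduled follow-ups are set out for women with a clinical pregnancy, so for a purely ectopic pregnancy, or a treatment complication without pregnancy, general adverse event reporting is the remaining route.

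**Working it through.** The point is mainly a comparison of passages. Arithmetic only gives a scale.

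**1. The list against typical events**

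| Event (no death, lasting disability or immediate threat to life) | Fixed criterion met? | Serious only by local discretion? | Other capture |
|---|---|---|---|
| Admission for pre-eclampsia | No | Yes | Adverse event record; scheduled follow-up; secondary outcome |
| Admission for postpartum haemorrhage | No | Yes | Adverse event record; delivery and postpartum follow-up; secondary outcome |
| Admission for ectopic pregnancy, no intrauterine sac | No | Yes | Adverse event record. Ectopic pregnancy is named for collection at about 13 weeks, but the follow-up schedule applies to clinical pregnancies |
| Newborn admission, no malformation, infant survives | No | Yes | Adverse event record; neonatal follow-up; secondary outcome |

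**2. Does another step close the gap?** The ethics committee is to decide whether an event is likely to be associated with the drug. That is relatedness, not seriousness. The data monitoring committee oversees safety, but the article does not say that it reclassifies events. No arm-blinded review of seriousness is described.

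**3. The plan's sample size, which supplies the base**

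Inputs from Sample size and Data analysis: 65% and 40.8%, two-sided alpha 0.05, power 80%, equal groups.

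n per group = [1.960 × √(2 × 0.529 × 0.471) + 0.842 × √(0.65 × 0.35 + 0.408 × 0.592)]² / 0.242² = 65.6, rounded up to 66.

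With 10% drop-out: 66 / 0.9 = 73.3, rounded up to 74 per group, 148 in total. Both figures reproduce.

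**4. Expected clinical pregnancies**

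- At 66 per group: 66 × 0.65 + 66 × 0.408 = 42.9 + 26.9 = 69.8.
- At 74 per group: 74 × 0.65 + 74 × 0.408 = 48.1 + 30.2 = 78.3.

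The lower base is the better one, because the rate is defined among women who received a transfer, and the 74 allows for drop-out.

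**5. Women whose classification would be discretionary**

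The documents give no admission rate. Assume 5–15% of clinical pregnancies involve an antenatal or early-pregnancy admission.

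- Base 69.8: 3.5 to 10.5 women.
- Base 78.3: 3.9 to 11.7 women.

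Purely ectopic pregnancies are not in either base and would add to the count.

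**6. Women outside the scheduled follow-up**

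At 66 per group, 132 − 69.8 = 62.2 women would have no clinical pregnancy. This is the size of the group that depends on general adverse event reporting, not a number of events.

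**The case against.** The strongest reply is that the safety comparison does not depend on the serious label, and that is correct. Pregnancy, perinatal and neonatal complications are secondary outcomes. They are collected at the same times in both arms and tested by chi-square or Fisher's exact test, with no seriousness decision involved. All adverse events are recorded whatever their cause, an independent committee reviews safety regularly, and the article plans no test of serious events between arms. A reader might infer that an arm-aware threshold could create or hide a difference in the trial's safety result. The documents do not support that.

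Other parts of the reply also stand:

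- The list is open. The discretionary clause allows any admission to be called serious.
- The Discussion sentence on pre-eclampsia and haemorrhage compares programmed with natural cycles, not with letrozole. The link to these two regimens rests on the separate statements about hypertensive disorders.
- Ovarian hyperstimulation should not be used as an example. The Background says only that frozen transfer reduces it and does not tie it to either regimen.
- An admission criterion does not remove all arm-aware judgement, because the decision to admit is also made unblinded.

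It can also be said that the article condenses a full protocol. This limits certainty but does not dispose of the point: the article prints the definition, and the item is not in it. Nor does capture as a secondary outcome help with speed of reporting, or reach women without a clinical pregnancy.

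**Conclusion.** The concern holds in a limited form. As written, hospital admission is serious only by local discretion at six open-label sites, and only serious events are stated to go to the principal investigator immediately. Admissions may therefore miss immediate reporting and be classified inconsistently between sites. What is at risk is seriousness classification, prompt reporting and a descriptive table of serious events. The secondary-outcome comparison is not at risk.

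The size is about 3 to 12 women, resting on the plan's assumed pregnancy rates and on an assumed 5–15% admission rate that the documents do not give. In a trial of 148, a few reclassified events would visibly change a table of serious events. It is tempting to conclude that classification will differ by arm. Unblinded judgement makes that possible, but nothing in the documents shows it.

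This is worth correcting, since the change is small. It is not a threat to the trial's main conclusions.

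**What to change.** Add one criterion to the list in the Follow-up plan: *inpatient hospital admission or prolongation of admission of the woman or the infant, other than routine admission for delivery*. With it:

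- apply the criterion alike in both arms and at all sites;
- keep the investigator's discretion as an addition to the fixed criteria;
- report serious events by arm irrespective of judged relatedness;
- reclassify adverse events already recorded where admission status is available.

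The cost is one line of text, more serious-event forms and some retrospective review. About half the women had been enrolled when the article was written, and the article does not say whether admission status was captured for them, so reclassification may be incomplete. What counts as routine admission for delivery also needs a short agreed definition, or the judgement simply moves there.

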### Data management

The data originates mainly from medical records and follow-up records. We use an electronic data capture (EDC) system to record and deposit the study data. Researchers will verify the original data and then data entry staff will enter it into the EDC after receiving professional training, which significantly ensures the accuracy of the input data. Consent forms, screening and identification records, and other participant-identifiable data will all be stored in site files and only researchers with permission can be able to access them. Paper files will be kept in a locked filing cabinet in the treating hospital. Electronic documents will be stored in a password-protected computer, with access restricted to the principal investigator. All research documents will be preserved for at least 5 years after publication.

### Independent Data Monitoring Committee (DMC)

An independent DMC has been appointed for this trial to oversee the safety monitoring. The DMC will review on a regular basis accumulating data from the ongoing trial and monitor the continuing safety of current participants and those yet to be recruited, as well as reviewing the validity and scientific merit of the trial.

The DMC composition, name, title, and address of the chairman and of each member are given in the DMC Charter which is in line with that proposed by the DAMOCLES Study Group [11]. Membership includes expertise in the relevant field of study, statistics, and research study design.

The DMC Charter includes, but is not limited to, defining the following: (1) the schedule and format of the DMC meetings, (2) the format for the presentation of data, (3) the method and timing of providing interim reports, (4) stopping rules.

The DMC is independent of the sponsor, Ethics Committees, regulatory agencies, investigators, clinical care of the trial participants, and any other capacity related to trial operations. The DMC has the responsibility for deciding whether, whilst randomization is in progress, the unblinded results (or the unblinded results for a particular subgroup) should be revealed to the researchers. The DMC Charter states that they will do this if, and only if, two conditions are satisfied: (1) the results provide proof beyond reasonable doubt that treatment is on balance either definitely harmful or definitely favourable for all, or for a particular category of, participants in terms of the major outcome and (2) the results, if revealed, would be expected to substantially change the prescribing patterns of clinicians who are already familiar with any other trial results that exist. Exact criteria for ‘proof beyond reasonable doubt’ are not, and cannot be, specified by a purely mathematical stopping rule, but they are strongly influenced by such rules. The DMC Charter is in agreement with the Peto-Haybittle [11, 12] stopping rule whereby an interim analysis of a major endpoint would generally need to involve a difference between treatment and control of at least three standard errors to justify premature disclosure. An interim subgroup analysis would, of course, have to be even more extreme to justify disclosure. This rule has the advantage that the exact number and timing of interim analyses need not be pre-specified. In summary, the stopping rules require extreme differences to justify premature disclosure and involve an appropriate combination of mathematical stopping rules and scientific judgement.

### Data analysis

All the generated data in the trial will be analysed by blinded independent biostatisticians. The primary analysis will be performed according to the intention-to-treat (ITT) principle. The Statistical Package for the Social Sciences (version 24.0; SPSS Inc., USA) will be used for all analyses. All tests will be two-tailed, and a *P* value < 0.05 is considered to be statistically significant. The primary outcome, clinical pregnancy rate, will be analysed using the chi-square test. The secondary outcomes such as abortion rate, live birth rate, and some complications will be analysed using the chi-square test or Fisher’s exact test for expected frequencies less than 5. The other parameters will be analysed and compared according to the following methods. The Shapiro-Wilk test will be used to test the normal distribution of continuous variables. For normally distributed data, we will use Student’s *t*-test to examine the differences between groups; for non-normally distributed data, we will use the Wilcoxon rank-sum test. Continuous variables will be represented as means ± standard deviations. Categorical variables will be described as frequencies or percentages, and the chi-square test or Fisher’s exact test is used to examine the differences between groups.

We will perform a secondary per-protocol analysis according to the actual treatment that subjects received who comply with the protocol. The data analysis methods are as above.

Missing data will be treated as missing at random and will be imputed using the last observation carried forward method. For the missing values, a sensitivity analysis will be done under the hypothesis of the worst and the best outcomes for each missing individual. Therefore, all secondary per-protocol analysis outcomes will be considered exploratory. All statistical analyses will be done using the statistical package SPSS (version 24.0; SPSS Inc., USA).

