### Sample size

The PASS software version 15.0.5 (NCSS, LLC, Kaysville, UT, USA) was used to estimate the sample size. We assumed that the clinical pregnancy rate is 65% in the letrozole ovulation regimen group and 40.8% in the programmed regimen group based on past retrospective investigations [6]. To detect an absolute difference in CPRs, the study will involve 66 women in each group with a power of 80% and an alpha error of 0.05. Considering a 10% follow-up drop-out rate, our target sample size will be 148 women.

To minimize the loss of follow-up, we optimize our strategies of follow-up, including text messaging reminders to patients’ mobile phones the day before scheduled appointments, reducing the number of clinic visits if possible, and regular review of patients with missed appointments to allow early contact and intervention.

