### Outcome and outcome assessments

The primary outcome is the clinical pregnancy rate, defined as the ratio of the clinical pregnancy (intrauterine gestation sac) number to the number of patients who received embryo transfer. The secondary outcomes include abortion rate, live birth rate, birth weight, pregnancy and perinatal complication, and neonatal complication.

Two weeks following embryo transfer, serum β-HCG is tested; a result of ≥ 10 IU/L indicates biochemical pregnancy. The patients who are biochemically pregnant will keep taking medications for luteal support. The existence of a gestational sac within the uterine cavity is referred to as clinical pregnancy. When the embryo implants anywhere other than the uterine cavity, it is referred to as an ectopic pregnancy. Around 5 weeks following embryo transfer, a transvaginal ultrasound is carried out to confirm clinical pregnancy. When a viable fetus with a fetal heartbeat is detected by ultrasound around 10 weeks following embryo transfer, it is considered to be an ongoing pregnancy.

Abortion rate is defined as the ratio of the number of nonviable pregnancies before 28 weeks of gestation to the number of clinical pregnancies. Abortion before 12 weeks of pregnancy is called early abortion while after 12 weeks of pregnancy is called late abortion. Live birth rate refers to the ratio of the number of normal fetuses delivered at 28 weeks or later of gestation to the number of patients who received embryo transfer. Preterm birth occurs between 28 and 37 weeks of gestation. A birth at 37 weeks or later is called a full-term birth. The congenital malformations are diagnosed after birth.

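### Birth weight: the test is chosen by a Shapiro-Wilk pre-test, but means and SDs are shown either way, so the P value may not test the means displayed or hold 5% if spread or shape differs between arms

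*Protocol article*

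**What the plan says.** In the Data analysis section, the primary outcome has its own fixed test: "The primary outcome, clinical pregnancy rate, will be analysed using the chi-square test". Binary secondary outcomes get chi-square or Fisher's exact test. For everything else, "The other parameters will be analysed and compared according to the following methods".

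Those methods begin with a pre-test: "The Shapiro-Wilk test will be used to test the normal distribution of continuous variables". Normally distributed data go to Student's t-test; "for non-normally distributed data, we will use the Wilcoxon rank-sum test". The section does not give the significance level of the pre-test, or say whether it is applied to each arm, to pooled data or to residuals.

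The summary statistic does not depend on the branch: "Continuous variables will be represented as means ± standard deviations".

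Birth weight is not named in the Data analysis section. It comes under the rule because the outcome section lists it: "The secondary outcomes include abortion rate, live birth rate, birth weight, pregnancy and perinatal complication, and neonatal complication".

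**The concern.** Three features of the stated rule matter for birth weight.

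1. **The hypothesis depends on the data.** Student's t-test addresses equal means; the rank-sum test addresses equal distributions. Which one the P value refers to is known only after the pre-test.
2. **Test and summary can part company.** After the rank-sum branch, the table would show two means and two SDs beside a P value that does not test the difference between those means.
3. **Student's t-test pools the variances.** That is harmless with equal numbers per arm. With unequal numbers and unequal SDs, the standard error is wrong. The trial plans for unequal numbers: the Sample size section assumes that the "clinical pregnancy rate is 65% in the letrozole ovulation regimen group and 40.8% in the programmed regimen group", so more births are expected in the letrozole arm.

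At stake is whether a nominal 5% P value for birth weight can be read as evidence about the mean difference shown.

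**Working it through.** **Inputs from the protocol article.** Clinical pregnancy 65% vs 40.8%; 66 women per group; 80% power; two-sided 0.05; 10% drop-out; 148 in total; 1:1 allocation. The document gives no SD, effect, number or power for birth weight.

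**The plan's own figure.** With p̄ = (0.65 + 0.408)/2 = 0.529 and d = 0.242:

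n = [1.960·√(2·0.529·0.471) + 0.842·√(0.65·0.35 + 0.408·0.592)]² / 0.242² = (1.384 + 0.576)² / 0.0586 ≈ 65.6, so 66 per group. Then 66/0.9 = 73.3, so 74 per group and 148 in total. Both figures reproduce.

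**Births per arm.**
- With 74 per arm and 85% of clinical pregnancies delivered (assumed): 74 × 0.65 × 0.85 = 40.9 and 74 × 0.408 × 0.85 = 25.7, so 41 vs 26.
- With 66 per arm and one birth for every clinical pregnancy: 66 × 0.65 = 42.9 and 66 × 0.408 = 26.9, so 43 vs 27.

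**Why pooling matters, by arithmetic.** Assume SD 400 g (n = 41) vs 600 g (n = 26).
- Pooled variance: (40·400² + 25·600²)/65 = 236,923. Squared standard error used by Student: 236,923 × (1/41 + 1/26) = 14,891.
- True squared standard error: 400²/41 + 600²/26 = 17,749.
- Ratio of standard errors: √(14,891/17,749) = 0.916. The critical value 1.997 (65 df) acts like 1.997 × 0.916 = 1.83, a normal-approximation error of about 6.7%.
- SDs reversed: Student uses 17,792 against a true 14,934, a ratio of 1.09. The effective critical value is 2.18 and the error about 2.9%.

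**Simulation.** True means are equal and tests are two-sided at 5%. The assumed rule is Shapiro-Wilk in each arm at 0.05, with rank-sum if either arm rejects and otherwise Student. All birth-weight distributions are assumptions.

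43 vs 27 births, 40,000 trials per row (simulation error about 0.1 point):

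| Scenario | Planned rule | Student always | Rank-sum always | Welch always |
|---|---|---|---|---|
| Normal, same SD | 5.1% | 5.0% | 5.0% | 4.9% |
| Preterm-tail mixture, same in both arms | 5.3% | 5.0% | 5.0% | 5.0% |
| Twin mixture, same in both arms | 5.3% | 5.0% | 4.9% | 5.0% |
| Lognormal, same in both arms | 5.0% | 4.7% | 4.9% | 4.9% |
| Normal, SD 500 (n = 43) vs 750 (n = 27) | 7.5% | 7.4% | 6.5% | 5.0% |
| Normal, SD 750 (n = 43) vs 500 (n = 27) | 3.5% | 3.2% | 4.2% | 4.9% |

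With the same unequal SDs but equal numbers, the planned rule gives 5.0% (30 vs 30) and 5.4% (40 vs 40), from 8,000 trials each.

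Runs with 41 vs 26 births, and one equal-number contrast, used fewer trials (6,000 to 20,000 where the count is recorded). Ranges show the spread between runs:
- SD 400 vs 600 g, no preterm births: planned rule 6.7 to 7.8%, Student alone 6.7 to 7.7%, Welch 5.0%.
- SDs reversed: planned rule 3.5 to 3.6%.
- 5% vs 20% preterm-like births (mean 2200 g, SD 500 g), overall mean 3250 g in both arms: planned rule 8.9 to 10.6%, rank-sum alone 10.4%, Student alone 7.1%, Welch 5.1 to 5.4%.
- The same 5% vs 20% mixture with 33 vs 33 births: planned rule 8.4 to 9.4%, Student alone 5.2 to 5.4%, Welch 5.1 to 5.4%.

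**Reading.** With one common distribution, the pre-test adds at most about 0.3 points. With unequal SDs, the planned rule and Student alone nearly coincide, so pooling explains the error. Only when shapes differ does the switch add its own error. The 33 vs 33 runs isolate this, because pooling does no harm at equal numbers.

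**The case against.** The strongest reply has four parts.

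**The pre-test is not the main cause.** A reader might infer that screening with Shapiro-Wilk generally inflates the false-positive rate. The figures do not support that: the rule gives 5.0 to 5.3% under a common distribution, and with unequal SDs Student's test alone is off by almost the same amount. This stands. Deleting the pre-test while keeping Student's t-test would change little in the unequal-SD cases.

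**The 9 to 10% scenario is not null for the rank-sum test.** To hold both means at 3250 g, term-like means must be (3250 − 0.05·2200)/0.95 = 3305 g and (3250 − 0.20·2200)/0.80 = 3513 g. The arm with more preterm-like births therefore has term babies about 207 g heavier. The distributions truly differ, and a rank-sum rejection is correct under its own hypothesis. This also stands: the figure is an error only if the P value is read as a test of the means, which is how the planned mean and SD display invites it to be read.

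**The direction is not known.** The Background cites a meta-analysis in which ovulation induction reduced preterm labour, which would suggest wider spread in the smaller programmed arm. But no birth-weight SD or preterm rate is given, and reversing the SDs makes the rule conservative.

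**The rule is fixed in advance and applied by blinded statisticians.** A reader might infer freedom to choose the more favourable test. The text gives no support for that. The rule is an algorithm, although the level and unit of its pre-test are not stated.

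What survives is the mismatch between test and display, and an error rate that depends on features of birth weight the trial cannot know in advance.

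**Conclusion.** The point holds as a minor one. The mismatch follows from the text alone: after the rank-sum branch, birth weight would carry a P value that does not test the means displayed.

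The size of the error is conditional. The figures of about 7 to 8%, about 3.5% and about 9 to 10% rest on assumed SDs, preterm shares and delivery rate, and on a pre-test applied per arm at 0.05. Only the inequality of birth numbers has a basis in the document, through the assumed pregnancy rates. The safe statement is that the planned rule holds about 5% when the arms share one distribution and may be too high or too low otherwise, while Welch remains at 4.9 to 5.4% in every scenario examined.

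Nothing here reaches the chi-square analysis of clinical pregnancy, the sample size or the power. Birth weight is one of several secondary outcomes and carries no power claim.

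**What to change.** In the Data analysis section:

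- Drop the Shapiro-Wilk selection step for birth weight.
- Pre-specify the unequal-variance (Welch) t-test, reported as a mean difference with 95% CI whatever the shape of the data.
- Keep the rank-sum test as a labelled sensitivity analysis.
- Report median and interquartile range for skewed variables and wherever a rank test is reported.

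The cost is about two sentences and a negligible loss of power if the variances are equal. There is no effect on sample size, data collection or the primary analysis. The change should be made before the birth-weight data are analysed by arm.
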